### Study 3: Implementation Study

#### Data Analysis

Descriptive statistics will be used to report usage of the TEN website and TEN Clinic over the 3-month period both pre- and postimplementation strategy. The *t* test will be used to compare overall usage of the TEN service for these 2 periods. Linear mixed models will examine latent growth in service usage following the implementation strategy.

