**Objective:**

The primary objective of this implementation study is to design and test an implementation strategy to improve uptake of TEN. The secondary objectives are examining the acceptability of TEN among HCWs, changes in mental health outcomes associated with the use of TEN, and reductions in mental health stigma among HCWs following the use of TEN.

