**Results:**

The implementation strategy, designed with input from the consultation and observational studies, is expected to lead to an increased number of unique visits to the TEN website in the 3 months following the introduction of the implementation strategy. The observational study is expected to observe high service acceptability. Moderate improvements to general mental health (DQ-5, WSAS) and a reduction in workplace- and treatment-related mental health stigma (EASI) between the baseline and 1-month time points are expected.

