## Methods

### Study Design

This study will follow an implementation-effectiveness hybrid design [24]. The protocol has 3 components (Figure 2). The *consultation study* component (Study 1) is a series of semistructured qualitative interviews conducted with stakeholders to explore the needs of Australian HCWs and develop an implementation strategy for TEN. The *observational study* component (Study 2) is a pre-/postobservational study with Australian HCWs evaluating the acceptability TEN, providing feedback on the implementation strategy, and examining any changes in mental health outcomes that are associated with use of the service. The *implementation study* (Study 3) component will be a pre-/postaudit of TEN users both before and after the implementation strategy is implemented [25].

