#### Data Collection

Quantitative data will be collected through an audit of usage of the TEN website and TEN Clinic for a period of 3 months both before and after the implementation of the implementation strategy. Although the exact implementation strategy will be determined by the results of the consultation study, example strategies from the literature include identifying “champions” within an organization to drive uptake or develop incentives, such as continuing professional development activities [32]. TEN website data include completed online assessments automatically recorded on UNSW servers and website analytics (eg, number of unique users, pages viewed) automatically collected through the SAS CI 360 platform. TEN Clinic data include service analytics data, which are routinely captured by clinicians in the delivery of TEN Clinic services. Surface-level nonidentifiable TEN Clinic data will be examined as part of the implementation study (eg, number of referrals, number of consultations).

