### Potential Limitations

Although the implementation strategy has not yet been designed, the wide availability of TEN makes it difficult to examine site- or specialization-specific implementation strategies or service upgrades. Although the goal of TEN is to provide a blended care service for all Australian HCWs, this lack of specificity may hamper implementation within specific HCW specializations. The future of blended health is platforms that can be easily customized to different contexts, allowing for tailored implementation strategies and service upgrades. Similarly, the broad aims of the implementation of TEN may not be easily generalizable to other, more specific, contexts.

This implementation study and observational study will also be carried out during the ongoing COVID-19 pandemic. TEN itself was designed to support the mental health of HCWs during the pandemic. As such, changes in the COVID-19 context in Australia, such as outbreaks, restrictions, and the vaccination rollout, are likely to affect both uptake of the service and mental health outcomes. Such wider events will be considered when interpreting the results of both the implementation strategy and the observational study.

The observational study is also limited by a lack of an appropriate control arm and use of randomization. Common mental health outcomes, such as distress, anxiety, and depression, have the potential to improve over time without intervention. Although subgroup analyses examining usage of the service may shed some light on improvement without the use of the TEN service, the fact remains that a randomized controlled trial design with a suitable control would provide more robust data on efficacy.

Due to common concerns around mandatory reporting among HCWs [34], the TEN website was designed to be accessed anonymously (ie, without registration). Although this is a strength of the service itself, it poses problems for measuring participant engagement with the TEN website during a prospective study. The method used in the observational study—providing users with a unique website link—is error prone. Although participants are asked to bookmark the link and will be provided with the link via email, it remains that participants may simply access the TEN website without using their unique link. During data analysis, participant website analytics will be compared against self-reported usage to understand the extent of such errors.

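### Study 3 tests the primary objective with a before/after t test in one uncontrolled series, which cannot separate the strategy from a background trend or allow for serial correlation

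*Protocol article*

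**What the plan says.** The Abstract states: "The primary objective of this implementation study is to design and test an implementation strategy to improve uptake of TEN". Study 3 is the component that does the testing. Under Study Design, this "component will be a pre-/postaudit of TEN users both before and after the implementation strategy is implemented". Under Study 3, Data Collection, usage of the website and clinic is audited "for a period of 3 months both before and after the implementation of the implementation strategy". No concurrent comparison series is described. The Abstract's Results paragraph gives the expected finding: the strategy "is expected to lead to an increased number of unique visits to the TEN website in the 3 months following" its introduction.

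The analysis is in Results, Study 3, Data Analysis. Usage in both periods is described. Then the *t* "test will be used to compare overall usage of the TEN service for these 2 periods". Finally, "Linear mixed models will examine latent growth in service usage following the implementation strategy".

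Potential Limitations acknowledges that "changes in the COVID-19 context in Australia, such as outbreaks, restrictions, and the vaccination rollout, are likely to affect both uptake of the service" as well as mental health outcomes, and says such events will be taken into account when the results are interpreted. No trend term, calendar or outbreak covariate, or correlation structure is stated for Study 3. The lack of a control arm is listed as a limitation of the observational study only.

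**The concern.** A two-sample t test compares two means and attributes the difference to the label that separates them. Here the label is calendar time. Any rise or fall already in progress therefore goes into the contrast along with any effect of the strategy. The test also treats each day or week as an independent observation. Successive counts from one website usually resemble their neighbours, so the standard error will tend to be too small.

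The document does not say what the test's unit is (day, week, month or user), and the consequence depends heavily on that choice. The growth model, as worded, concerns usage after launch. A post-launch slope on its own does not show whether the slope changed.

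At stake is the answer to the primary objective. Uptake that was already climbing, for example during an outbreak, could be credited to the strategy. Uptake falling as an outbreak subsides could mask a strategy that works.

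**Working it through.** **Plan's own figure.** There is none to reproduce. No effect size, alpha, power or number of observations is stated for Study 3.

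**Inputs.** From the document: two adjacent 3-month windows, one series, a t test between them. Assumed: 13 weekly points (or 91 daily points) per period; coefficient of variation (CV) 20% weekly or 30% daily; lag-1 correlation ρ from 0 to 0.7; linear background change of 10–50% over the 6 months. All tests are two-sided at 5%, and the strategy has no effect unless stated.

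**1. Bias from a linear trend.** If usage rises by *b* over 2*m* equally spaced points, the difference in period means is *b* × *m*/(2*m* − 1). For *m* = 13 this is *b* × 13/25 = 0.52*b*. The t test thus sees about half the 6-month drift as an effect.

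**2. Rejection rate from trend alone, weekly, ρ = 0.**
- A 30% rise with CV 20% is *b* = 0.30/0.20 = 1.5 SD, so the contrast is 0.52 × 1.5 = 0.78 SD.
- Its standard error is √(2/13) = 0.392 SD, giving 0.78/0.392 = 1.99.
- The trend also inflates the within-period SD by a factor of 1.027, which lowers this to 1.94.
- On 24 degrees of freedom, the probability of a significant increase is 46%. Simulation (20,000 series) also gives 46%.
- Other rises, by simulation: 10% gives 9%, 20% gives 24%, 50% gives 86%.
- Daily points with CV 30% and a 30% rise (1 SD): 92%.

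**3. Rejection rate from serial correlation alone, no trend.** For a long series the variance of a mean is inflated by about (1 + ρ)/(1 − ρ), so the false-positive rate is roughly 2 × [1 − Φ(1.96/√inflation)].

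| ρ | inflation | approximate rate | simulated, 13 v 13 weeks |
|---|---|---|---|
| 0 | 1.00 | 5% | 5% |
| 0.3 | 1.86 | 15% | 14% |
| 0.5 | 3.00 | 26% | 24–25% |
| 0.7 | 5.67 | 41% | 39–40% |

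**4. Masking.** A true gain of 20% of baseline (weekly, CV 20%, ρ = 0) is detected in 68–69% of series with no trend, but in 7% when there is a 30% background fall.

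**5. Post-launch slope only.** If the growth model used post-launch weeks alone, a simple slope test would be significant in 8% (1 SD trend) and 17% (2 SD trend) of null weekly series at ρ = 0.

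**6. The alternative, segmented regression.** With terms for pre-launch slope, level change and slope change, a linear background trend is absorbed and no longer biases the level change.
- If ρ were known, the level and slope tests each hold at 4–5% in every setting tried.
- With ρ estimated from 13 + 13 weeks, the level-change test rejects in about 9–15% of null series at ρ = 0–0.3. With 39 + 13 weeks it rejects in about 7–8%.
- If either the level or the slope change may count as success, the rates are 18–25% at 13 + 13 weeks and 12–17% at 39 + 13 weeks.

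**The case against.** **The growth model may use both periods.** The phrase about growth following the strategy states a question, not a data window. Data are collected before and after launch, and pre-launch data are not expressly excluded. This stands. A reader might infer that the model is fitted only after launch, but the text does not establish it. What can be said is that no pre-launch slope comparison is stated. The t test has the same weakness on either reading.

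**The authors have seen the confounding.** Potential Limitations promises to consider wider events at interpretation. So the document does not support saying that a trend *will* be read as an effect of the strategy. The safeguard is only qualitative, however, and does not correct an estimate or a p value.

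**Type I error far above 5% is not established.** This is also right as an unconditional claim. The document gives no trend, variability or correlation, and with none of these features the test holds at 5%.

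**Anonymous visitors do not rule out a repeated unit.** Site analytics include IP address and time of access, so some linkage over time may be possible. The case here does not rest on its absence.

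**The remedy is imperfect.** For autocorrelation alone at 13 + 13 weeks, segmented regression with estimated ρ (up to 15% at ρ = 0.3) is no better than the t test (14%). Its gain is against trend: about 9% rather than 46% at ρ = 0. This limits the remedy and is why the pre-launch series should be lengthened.

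**This could be left to a fuller plan.** Time unit and covariates could be. But the article names the between-period test, so this is a stated choice and not an omission. It is true that the t test is not labelled primary; the only analysis so labelled is the Study 2 model of WSAS change.

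**Conclusion.** The point holds in conditional form. The stated between-period comparison for the primary objective is a t test on one uncontrolled series. It credits about half of any linear 6-month drift to the strategy and makes no allowance for serial correlation, in a setting where the document itself expects uptake to move for other reasons.

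If trend or correlation is present, the false-positive rate exceeds 5%. Illustrative sizes for 13 against 13 weeks are 14–39% for ρ of 0.3–0.7 with no trend, and about 46% declaring an increase under a 30% rise with weekly CV 20% and no correlation. A 30% fall can cut detection of a real 20% gain from about 69% to 7%. These rest on assumed trend, CV, correlation and weekly units, and show direction and plausible range only.

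The document does not show that the growth model excludes pre-launch data, or that the authors would ignore the pandemic context when drawing conclusions.

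**What to change.** Rewrite the Study 3 Data Analysis before its ethics submission, which the document says is still to come.

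- Keep the 3-month before/after means and t test as description only.
- Make the main comparison a segmented (interrupted time-series) regression of weekly unique visitors over both periods, with pre-launch slope, level change and slope change.
- Pre-specify one primary contrast. Examples are the level change at launch, or the model-based difference from the projected pre-launch trend averaged over the 3 months. Do not allow either level or slope to count as success.
- Use errors that allow for autocorrelation, with a small-sample correction.
- Extend the pre-launch series as far back as existing analytics allow, since 13 + 13 weeks leaves the level test at about 9–15% false positives.
- Add indicators for outbreak and lockdown weeks as a sensitivity analysis.
- State that an event coinciding with launch cannot be separated from the strategy in this design.

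**Cost.** Revised analysis wording and an export of analytics that are captured automatically; no new data collection. How far back those analytics reach is an assumption, and a longer series leans harder on a linear pre-launch trend. Expect wider confidence intervals, lower power and possibly a less favourable result.

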## Discussion

### Summary

Blended digital and person-to-person care has significant potential to support mental health of HCWs through service flexibility and widespread availability. To date, however, the potential of blended care has been hampered by a lack of knowledge around the optimal implementation of such services. The CFIR framework provides a structured approach to implementation that will guide the development and application of implementation strategies for TEN. Using a implementation-effectiveness hybrid study, this implementation study will span 3 separate components. Through a series of consultations, an implementation strategy tailored to HCWs will be developed. Feedback on this strategy will be provided by HCWs participating in an observational study of TEN, from which data on the effectiveness of TEN will be acquired. Finally, the implementation strategy will be implemented and compared against the previous engagement strategies. The knowledge created by this project will inform the development and delivery of blended mental health services for HCWs, including how such services can be rapidly launched and implemented during times of crisis.

### Potential Limitations

Although the implementation strategy has not yet been designed, the wide availability of TEN makes it difficult to examine site- or specialization-specific implementation strategies or service upgrades. Although the goal of TEN is to provide a blended care service for all Australian HCWs, this lack of specificity may hamper implementation within specific HCW specializations. The future of blended health is platforms that can be easily customized to different contexts, allowing for tailored implementation strategies and service upgrades. Similarly, the broad aims of the implementation of TEN may not be easily generalizable to other, more specific, contexts.

This implementation study and observational study will also be carried out during the ongoing COVID-19 pandemic. TEN itself was designed to support the mental health of HCWs during the pandemic. As such, changes in the COVID-19 context in Australia, such as outbreaks, restrictions, and the vaccination rollout, are likely to affect both uptake of the service and mental health outcomes. Such wider events will be considered when interpreting the results of both the implementation strategy and the observational study.

The observational study is also limited by a lack of an appropriate control arm and use of randomization. Common mental health outcomes, such as distress, anxiety, and depression, have the potential to improve over time without intervention. Although subgroup analyses examining usage of the service may shed some light on improvement without the use of the TEN service, the fact remains that a randomized controlled trial design with a suitable control would provide more robust data on efficacy.

Due to common concerns around mandatory reporting among HCWs [34], the TEN website was designed to be accessed anonymously (ie, without registration). Although this is a strength of the service itself, it poses problems for measuring participant engagement with the TEN website during a prospective study. The method used in the observational study—providing users with a unique website link—is error prone. Although participants are asked to bookmark the link and will be provided with the link via email, it remains that participants may simply access the TEN website without using their unique link. During data analysis, participant website analytics will be compared against self-reported usage to understand the extent of such errors.

### Conclusion

By using a blended care approach, TEN can overcome common barriers to HCWs engaging with mental health services—primarily by allowing HCWs to anonymously access digital resources. Nonetheless, it remains that many HCWs will still choose not to engage with person-to-person services due to concerns around mandatory reporting. Further, although the lack of registration to access TEN ameliorates concerns around digital privacy, it requires computer skills that some HCWs may be lacking. Although these are issues beyond the scope of this evaluation, they need to be considered and addressed when designing and implementing mental health services for HCWs.

## Abbreviations

CFIR: Consolidated Framework for Implementation Research
DQ-5: Distress Questionnaire
EASI: Endorsed and Anticipated Stigma Inventory
GAD-7: Generalized Anxiety Disorder
HCW: health care worker
IP: internet protocol
OBI-16: Oldenburg Burnout Inventory
PCL-5: Posttraumatic Stress Disorder Checklist
PHQ-9: Patient Health Questionnaire
PTSD: posttraumatic stress disorder
SAS CI 360: SAS Customer Intelligence 360
TEN: The Essential Network
UNSW: University of New South Wales
WSAS: Work and Social Adjustment Scale
